**4.3.7.1.1 - Stable patients**

Because complete survey data will be required on all stable patients prior to computed tomographic requests, these records will only be deleted if radiographic reports and need for neurosurgery are missing.

**4.3.7.1.2 - Unstable patients**

Unstable patients make up a small minority of minor blunt head injury victims. The exact proportion varies from hospital to hospital. This makes it impossible to accurately estimate how many of these patients may be entered into the study. Because physicians may defer complete data entry on unstable patients, it is possible that final records for some of these patients might be incomplete. However, in our selective cervical spine and previous head injury studies we found that less than 10% of the study patients were classified as unstable, and all of these patients had complete criteria assessments. Thus, missing data from unstable patients is unlikely to be a significant problem in this validation study. In addition, physicians will be required to supply a minimal amount of demographic information on these patients prior to tomographic request generation, and are requested (and required by protocol) to complete data entry on all patients (even though this data entry may be non-concurrent). Records containing incomplete data will not be used in validating the decision instrument. These entries *will* be used in descriptive analyses on the demographics and injuries patterns associated with mild head trauma. Cases missing tomographic reports and information regarding the need for neurosurgical intervention will be deleted from the study.

**4.3.7.2 - Mathematical calculations**

The following mathematical forms will be used in statistical analyses:

**4.3.7.2.1 - Sensitivity, specificity and negative predictive value**

Sensitivity, negative predictive value and specificity will be used to determining the performance of the decision instrument. These measures will be calculated using the following standard formulae:

Sensitivity
[figure not shown]
 Negative Predictive Value

[figure not shown]

Specificity

[figure not shown]

Where:

TP = Number of individuals with intracranial injury labeled positive by the decision instrument.

FN = Number of individuals with intracranial injury labeled negative by the decision instrument.

FP = Number of individuals with no intracranial injury labeled positive by the decision instrument.

TN = Number of individuals with no intracranial injury labeled negative by the decision instrument.

Confidence intervals for sensitivity, specificity and negative predictive value will be determined using exact limits for proportions [48]:

[figure not shown]

Where:

P_L_ = Lower confidence limit for the proportion being studied (i.e. the lower confidence limit for the negative predictive value or sensitivity of selective criteria).

X = Number of times the event of interest is observed.

N = Total number of observations.

α = Statistical confidence value (Set to 0.05).

ν_1_ = Degrees of freedom for the numerator; ν_1_ = 2 [ N - X + 1 ]

ν_2_ = Degrees of freedom for the denominator; ν_2_ = 2 X

F_α/2,ν1,ν2_ = One tailed value of the F-distribution with ν_1_ and ν_2_ degrees of freedom

[figure not shown]

Where:

P_U_ = Upper confidence limit for the proportion being studied.

X = Number of times the event of interest is observed.

N = Total number of observations.

α = Statistical confidence value (Set to 0.05).

ν′_1_ = Degrees of freedom for the numerator; ν′_1_ = 2 [ X + 1 ]

ν′_2_ = Degrees of freedom for the denominator; ν′_2_ = 2 [ N - X ]

F_α/2,ν′1,ν′2_ = One-tailed value of the F-distribution with ν′_1_ and ν′_2_ degrees of freedom.

The sensitivity and negativity predictive value will determine whether the decision instrument reliably identifies all patients with significant intracranial injuries. The true-negatives will reveal the number of patients who can safely forego radiographic imaging. Comparisons between injured and non-injured groups will be made by chi-square testing, or Fisher's exact test if any cell has less than 5 subjects. Bonferroni or other statistical adjustment will not be made for analyses performed for descriptive purposes.

**4.3.8 - Quality Assurance**

**4.3.8.1 - Protection of Survey Data**

The site liaisons will be charged with verifying compliance with study protocols at their institution. Specifically this will require the liaisons to verify that survey data on all patients who undergo computed head tomography is accurately entered into the computer database.

Coordinators will review the tomography logs on a weekly basis to verify that all blunt head trauma victims who have undergone computed head tomography have also been entered into the computer database at their site. Any omitted cases will be discussed with the emergency physicians for that site and an attempt to identify any protocol errors will be initiated. Omissions due to personnel non-compliance will result in counseling of the involved parties. Omissions due to mechanical, protocol or system problems will be handled by consultation with the principal investigator at UCLA. The UCLA investigator will then determine whether protocol corrections are needed and will direct the implementation of any changes. To minimize corruption of the study data, any cases omitted from the database due to personnel or system failures will be excluded from the study.

Site liaisons will also be responsible for verifying that data is being accurately entered into the computer. They will observe relevant cases as they are processed by the emergency department, and will verify that each patient is seen by a physician, that survey data is entered into the computer, and that computed tomography is obtain as specified by the protocol.

Quality assurance checks will also be randomly performed by the liaisons to verify that physicians are adhering to examination guidelines. The physician liaison will be responsible for verifying that appropriate physical examinations are being performed and recorded on all patients presenting to their site. Any violations of protocol or incomplete examinations will result in verbal counseling of the involved parties and re-education in proper technique. Repeat flagrant violations will result in suspension of data collection by the involved physician. All records produced by a suspended physician will be reviewed and any suspect cases will be deleted. These physicians will still be able to obtain emergent tomographic imaging by attaching their name and the patient’s hospital number on a pre-generated waivers. These waivers will be enable CT requisition without survey entry, and will enable technicians to perform the needed imaging. Liaisons will collect the waivers during their routine quality assurance assessments and ensure that they are being used sparingly, and only by the suspended physician. Misuse of the waivers will result in termination of data collection at the involved institution.

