Injuries such as isolated linear or basilar skull fractures, solitary small cerebral contusions, localized subarachnoid hemorrhage less than 1 mm thick, thin subdural hematomas less than 4mm thick, isolated pneumocephaly, and closed depressed skull fractures that do not violate the inner table will not be considered to be significant injuries [63]. Coincidental or congenital abnormalities will also not be considered to be significant intracranial injuries. Chronic subdural hematomas, without evidence of acute change, will be considered to be coincidental injuries and will not be considered to be significant acute injuries. Chronic subdural hematomas that exhibit any recent change, or those that are of indeterminate age, will be considered to be acute significant injuries.

Research assistants, blind to classification by the decision rule, will review the medical records of patients with positive tomographic scans to determine whether or not the patient received neurosurgical intervention. The need for neurosurgical intervention is defined as any of the following within seven days of the initial injury [63]:

1 – Death due to intracranial injury.

2 – Intubation for management or support of head injury.

3 – Craniotomy, elevation of skull fracture or intracranial pressure monitoring.

Cases involving death or intubation will be reviewed by the physician liaison to determine, on the basis of their best clinical judgment, whether there was a causal relationship between the event and the patients intracranial injury. The liaisons will be instructed to consider these events as causally related to intracranial injury unless there is compelling evidence to the contrary. Patients will not be considered to have received neurosurgical intervention if their death is clearly due to causes unrelated to their head injury, or if they were intubated solely to expedite care.

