**4.3.6 - Database Management**

A database application will be used to display the data questionnaire, provide input fields for survey responses, and direct storage and management of study data. This system will employ a redundant entry system that requires each response to be recorded twice. Discrepancies between responses will generate a prompt that will require the data to be re-entered until concordant responses are recorded. This process will help minimize the potential for data corruption from keyboard entry errors. Our database applications have been previously developed, tested and implemented in the prior studies on selective criteria in cervical spine injury and selective tomographic imaging in blunt head trauma. Captured data will be initially stored in a database file on the microcomputer hard disk drive until the next weekly data transfers and concatenation. In addition to data transfers, data will remain in each system, to serve as an ultimate backup, until completion of the entire study. Once a complete survey form has been entered into the database it will be unalterable by the affiliated site hospital. Error correction will follow the protocols described below. The examining clinicians will have access only to survey entry forms, while site liaisons and coordinators, and UCLA data analysts will be able to examine and transmit entire data sets.

A multi-functional database management application and programming language will be used as the main database management tool to create, store, maintain and analyze data records. This application will be used to program file maintenance utilities (i.e. concatenating programs, search routines, error detection programs, etc.), and its analytic capabilities will be used extensively in data analyses.

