**4.3.8.2 - Protection of Radiographic Data Integrity**

Preliminary diagnoses of "no injury" will be confirmed in two ways. First, quality assurance logs, which contain lists of significant radiological findings that were missed on preliminary reading, will be reviewed by the site liaisons during routine evaluations. Any revisions found on these surveys will be transmitted to UCLA where they will be incorporated into the study database. Second, the diagnoses of all blunt trauma patients admitted through the emergency department and discharged from the hospital during and up to three months after each study period will be searched and all intracranial injury cases identified. The charts of such patients will be reviewed to determine if the case was included in the study (using the patient number previously printed on the redacting forms), and if so, whether the case was classified as having an intracranial injury (based on whether the leaf was marked). The liaisons will notify core UCLA personnel of any cases of missed injury detected in this fashion. These cases will be reviewed by the site liaisons to determine, based on their best judgment, whether they involve protocol errors, and whether they represent a false-negative event (patient with a head injury, but “low-risk” according to the decision instrument). Site coordinators will notify core UCLA personnel of their findings. Reviews of the quality assurance logs and discharge diagnoses will be performed by the site liaisons on a bi-monthly basis.

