**5 - Research Assistant**

The research assistant will maintain the central UCLA database. Duties will include:

•Reviewing and concatenating survey data received form each of the study sites.

•Abstracting and concatenating radiographic reports and survey data.

•Assisting in software updates and data analysis.

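### Records already entered by a suspended physician may be deleted as suspect with no stated criterion, no blinding and no analysis that keeps them, in a study whose target allows no miss

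*Protocol*

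**What the plan says.** Section 4.3.8.1 of the protocol has site liaisons check that physicians follow the examination guidelines. A first violation leads to counselling. After that, "Repeat flagrant violations will result in suspension of data collection by the involved physician", and then "All records produced by a suspended physician will be reviewed and any suspect cases will be deleted". The section does not define a suspect case, name the reviewer, state what information the reviewer may use, or require a log or an analysis that retains the deleted cases.

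Other sections show what the likely reviewers can see:

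- Section 4.3.6: "site liaisons and coordinators, and UCLA data analysts will be able to examine and transmit entire data sets".
- Section 4.3.5.1.2, on outcome: "Cases involving death or intubation will be reviewed by the physician liaison".
- Section 4.3.8.2: liaisons review injuries found later and use their best judgment on "whether they involve protocol errors, and whether they represent a false-negative event".
- Section 5.2: a file linking record numbers to study numbers is available to research personnel until quality assurance is finished.
- Appendix E, among the central research assistant's duties: "Abstracting and concatenating radiographic reports and survey data".

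Blinding to the rule is stated for the radiologists and for the research assistants who establish neurosurgical intervention (4.3.5.1.2). It is not stated for the deletion review.

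The numerical target is in sections 2 and 3.2: 368 neurosurgical cases, all detected, for a lower confidence limit of 99.0%. Section 4.3.10.3 continues enrolment until there are 368 such cases, unless 10 misses occur first.

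**The concern.** Deleting records after entry is harmless to the estimate only if the decision does not depend on the combination of instrument result and outcome. Here nothing prevents that dependence. When a careless physician's forms are reread, an all-absent form on a patient who later had a craniotomy is the one most likely to look like an inadequate examination. A form with a criterion ticked, from the same physician and the same kind of patient, counts as a detection and is less likely to attract attention. This direction is a judgment about how such reviews tend to go, not something the protocol states, and it needs no bad faith. If it happens, false negatives leave the data more readily than true positives, and sensitivity and negative predictive value move toward the study hypothesis.

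The rule also sits awkwardly with the protocol's own safeguards. Section 4.3.6 makes a completed survey unalterable by the site. Section 4.3.8.3 keeps an erroneous original until final concatenation and codes its replacement, to guard against tampering. The suspect-case deletion has no such trail, so a reader of the final report could not tell whether a result of 368/368 depended on it.

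**Working it through.** **Inputs.** α = 0.05, used as α/2 in the exact limit (3.2 and 4.3.7.2.1). Target lower limit 0.99, 368 cases with no miss, prevalence 1.2% (3.2). Stop at 10 misses (4.3.10.3).

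**The plan's own figure.** With X = N the exact lower limit reduces to P_L = (α/2)^(1/N). Setting P_L = 0.99 gives N = ln(0.025)/ln(0.99) = 367.04, rounded up to 368. Enrolment is 368/0.012 = 30,667, in line with the stated 31,000. The plan's figures reproduce.

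**Effect of one or two records.** Exact lower limits from the protocol's F formula:

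| Situation | Detected/cases | Lower limit |
|---|---|---|
| No miss | 368/368 | 99.003% |
| One miss, kept | 367/368 | 98.50% |
| One miss, deleted, not replaced | 367/367 | 98.9999% |
| One miss, deleted, enrolment continued and next case detected | 368/368 | 99.003% |
| Two misses, kept | 366/368 | 98.05% |
| Two misses, deleted, not replaced | 366/366 | 98.997% |

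Deletion without replacement leaves the limit just under 99.0%, and it reaches 99.0% only on rounding. Deletion with replacement meets the target outright, and the enrolment rule in 4.3.10.3 permits replacement. With the miss kept, 99.0% is first reached at 555 cases, which is 555/0.012 = 46,250 patients.

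**How often the route could matter.** The documents do not give the inputs, so these are assumptions for illustration: true sensitivity 99.5%, suspended physicians holding 1% to 5% of the neurosurgical cases, and every one of their misses deleted.

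- Expected misses in 368 cases: 368 × 0.005 = 1.84.
- Chance of no miss with nothing deleted: 0.995^368 = 15.8%.
- Chance that no miss remains after deletion, at a 1% share: 0.995^(368 × 0.99) = 16.1%.
- At a 5% share: 0.995^(368 × 0.95) = 17.3%.
- If the suspended physicians' sensitivity is 97.5% (five times the miss rate), the chance of no miss without deletion is 0.1610 × 0.975^3.68 = 14.7% at a 1% share and 0.1734 × 0.975^18.4 = 10.9% at a 5% share. Deletion then adds about 1.4 and 6.5 percentage points respectively.

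So the effect on a single record is decisive, while the chance of it arising is small to moderate.

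**The case against.** The case on the other side is substantial, and several parts of it stand.

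- *The trigger does not depend on outcome.* Suspension follows repeated flagrant violations found by random checks, only that physician's records are exposed, and section 3.1 reports good compliance in the earlier study. This stands and makes the route narrow. A zero-miss result would need every miss to lie among those records.
- *Unblinded review is not stated.* A reader might infer that the protocol assigns deletion to people who know the outcome. It does not; section 4.3.8.1 names no one. Section 4.3.4 also has index numbers destroyed after reports are collected. What can be said is that the form itself shows the criteria, and that sections 4.3.6, 4.3.8.2, 5.2 and Appendix E leave access to the outcome open.
- *Section 4.3.8.2 deletes nothing.* A reader might infer that it lets liaisons discard false negatives as protocol errors. The text does not say so. Its search looks for missed injuries, which works against the hypothesis. The mechanical false-negative rule in section 4.3.3.1 governs only the work-up bias cohort. For the main analysis, section 4.3.7.2.1 defines a false negative, and the liaison's judgment is simply not tied to it.
- *Section 4.3.3 withholds special training, but does not endorse examinations that were never done.* This stands. It would go too far to require every record of a repeat violator in the primary analysis.
- *The primary outcome is an estimate with an interval* (4.3.7), not a formal pass or fail. This is true, but section 2 speaks of validation in terms of roughly 368/368, so one miss still changes the claim that can be made.

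None of this supplies the missing criterion, blinding or retained-data analysis.

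**Conclusion.** The point holds in a limited form. Section 4.3.8.1 fixes a deletion rule that, followed as written, can bias sensitivity and negative predictive value upward. This is a rule fixed badly, not a detail left to an analysis plan. One record separates a lower limit of 99.003% from 98.50%, and a deleted miss could be replaced by further enrolment. The 10-miss stop does not say whether deleted misses count.

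The limits follow from the protocol's formula and do not depend on assumptions. The likelihood does: with true sensitivity of 99.5% and a 1% to 5% share of cases, deletion adds from under 1 to about 6.5 percentage points to the chance of a zero-miss result. A reader might infer that the protocol sets up outcome-dependent deletion or that misses will be removed. The documents support only that nothing prevents it and that no later reader could detect it.

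**What to change.** **Section 4.3.8.1.** Replace the deletion of suspect cases with this rule: records entered before suspension are flagged and stay in the database. A record may be excluded only for a process failure stated in advance, for example an examination that was not performed. The decision is made by existing staff blind to the rule classification, the CT result and the neurosurgical outcome, so it rests on quality-assurance observations and not on the completed form. It is applied uniformly to that physician's records over a stated period.

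**Reporting.** Give sensitivity and negative predictive value with and without the excluded records, and list the rule-by-outcome cell of each.

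**Section 4.3.10.3.** State that flagged misses count toward the 10-miss stop.

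**Section 4.3.8.2.** State that false-negative status follows the definition in section 4.3.7.2.1, applied to the criteria as recorded, and that protocol errors are reported and not used to remove cases.

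**Cost.** Wording changes and one extra table, with no new staff or data. The reported sensitivity may be slightly less favourable.

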**4.3.8.2 - Protection of Radiographic Data Integrity**

Preliminary diagnoses of "no injury" will be confirmed in two ways. First, quality assurance logs, which contain lists of significant radiological findings that were missed on preliminary reading, will be reviewed by the site liaisons during routine evaluations. Any revisions found on these surveys will be transmitted to UCLA where they will be incorporated into the study database. Second, the diagnoses of all blunt trauma patients admitted through the emergency department and discharged from the hospital during and up to three months after each study period will be searched and all intracranial injury cases identified. The charts of such patients will be reviewed to determine if the case was included in the study (using the patient number previously printed on the redacting forms), and if so, whether the case was classified as having an intracranial injury (based on whether the leaf was marked). The liaisons will notify core UCLA personnel of any cases of missed injury detected in this fashion. These cases will be reviewed by the site liaisons to determine, based on their best judgment, whether they involve protocol errors, and whether they represent a false-negative event (patient with a head injury, but “low-risk” according to the decision instrument). Site coordinators will notify core UCLA personnel of their findings. Reviews of the quality assurance logs and discharge diagnoses will be performed by the site liaisons on a bi-monthly basis.

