Criteria assessments, survey results and the contact information obtained on each follow-up patient will be retained in a secure, locked file that will be indexed using the coded study numbers. Data from this file will only be accessible to the research assistants and study administrators. Information from completed surveys and matching criteria assessments will be entered into a computer database for long-term storage, transmission and analysis. Data will be entered into the computer using a redundant input system where each data element is entered twice. This system will protect against keyboard and entry errors, and help ensure data integrity. The computer data will be indexed using the coded study numbers and will not contain information that could be used to identify individual patients. The final record for each patient will contain the patient’s age (if less than 90 years, or a 90+ designation for patients older than 90 years), sex, race, date of injury, presence or absence of each criterion, date of follow-up, whether the patient sought additional care, whether the patient received imaging (and if so, the type of imaging: skull films, CT, MRI), whether the patient received any treatment, whether the patient was admitted to the hospital for their brain injury, and whether the patient underwent a neurosurgical intervention (and if so, what type). All contact information and any linking patient identifiers will be destroyed once follow-up information has been obtained.

Research assistants will make weekly backup copies of the computerized database, at which time the data will be reviewed for exceptional events. Cases will be considered to represent false-negative events if the patient was classified as low risk by the decision instrument, yet required neurosurgery. Cases will be counted as true-positives if they required neurosurgery and were not classified as low risk by the decision instrument. The error in sensitivity produced by work-up bias will be determined by computing the difference between the true sensitivity, as measured among the entire cohort of head injured patients presenting to the UCLA site during the work-up bias assessment, and the sensitivity measured among patients from this site who were selected for imaging. The exact formula for this calculation is as follows:

[figure not shown]

Where:

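### The site liaison, who is not stated to be blind to the instrument result, rules on causality and on missed injuries; few cases are exposed, but one of them moves the primary lower limit from 99.0% to 98.5%.

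*Protocol*

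**What the plan says.** Blinding is explicit for two groups. Section 4.3.5.1.2 keeps the radiologists unaware of the instrument classification, and for chart review it states: "Research assistants, blind to classification by the decision rule, will review the medical records of patients with positive tomographic scans".

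Two rulings then go to the liaison, who under 4.3.1 is the emergency physician representing each site.

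- **Death and intubation (4.3.5.1.2).** These are components of the primary outcome definition. Such cases "will be reviewed by the physician liaison to determine, on the basis of their best clinical judgment, whether there was a causal relationship" with the intracranial injury. Liaisons are "instructed to consider these events as causally related to intracranial injury unless there is compelling evidence to the contrary".
- **Injuries found later (4.3.8.2).** Liaisons review missed injuries "to determine, based on their best judgment, whether they involve protocol errors, and whether they represent a false-negative event". A short parenthesis describes a false negative as an injured patient whom the instrument called low risk.

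On access, 4.3.6 says "site liaisons and coordinators, and UCLA data analysts will be able to examine and transmit entire data sets", and 4.3.8.1 has liaisons verify survey entry and observe cases. Section 4.3.8.3 gives entry codes only to coordinators and administrators.

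For un-imaged patients, 4.3.3.1 uses a fixed rule: "Cases will be considered to represent false-negative events if the patient was classified as low risk by the decision instrument, yet required neurosurgery".

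**The concern.** By blinding radiologists and chart reviewers, the protocol treats knowledge of the classification as a threat to outcome ascertainment. The discretionary calls that remain go to someone for whom no blinding is stated. In the 4.3.8.2 review blinding is not even possible, because the liaison is asked whether the patient was low risk.

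Whether a case is a false negative needs no judgment. It follows from the recorded criteria and the outcome, as 4.3.3.1 already says for un-imaged patients. The protocol-error question does involve judgment, but it is answered after the outcome is known, and no consequence is attached to the answer.

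At stake are the primary sensitivity (4.3.7) and the termination count (4.3.10.3). If a ruling made with knowledge of both classification and outcome takes a miss out of the count, the estimate moves upward and the stop comes later.

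**Working it through.** **1. Reproduce the plan's figure.** Inputs from 3.2: α = 0.05, α/2 in the exact limit, target P_L = 0.99, no misses (X = N). With X = N the exact limit reduces to P_L = 0.025^(1/N).

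- N = 367: 0.025^(1/367) = 0.989999
- N = 368: 0.025^(1/368) = 0.99003

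The smallest adequate N is 368, as stated. At 1.2% prevalence, 368 / 0.012 = 30,667, which agrees with the stated 31,000.

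**2. Effect of misses at N = 368.** Formula from 4.3.7.2.1: P_L = X / [X + (N − X + 1)·F], where F has 2(N − X + 1) and 2X degrees of freedom.

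| Misses | Sensitivity | Exact 95% lower limit |
|---|---|---|
| 0 | 100% | 99.00% |
| 1 | 99.73% | 98.50% |
| 2 | 99.46% | 98.05% |
| 3 | 99.18% | 97.64% |

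With one miss counted, 555 events would be needed to bring the lower limit back to 99.0%, or 555 / 0.012 = 46,250 patients.

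**3. What one ruling does to one true miss.**

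- Counted: 367/368, lower limit 98.50%.
- Taken out, with enrolment continuing to 368 events: 368/368, lower limit 99.00%.
- Taken out and not replaced: 367/367, lower limit 0.989999, which is 99.0% after rounding.

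For death or intubation, 4.3.5.1.2 states the consequence of a ruling of unrelated: the case is no longer an endpoint event. For a protocol-error label, 4.3.8.2 states no consequence, so the second and third lines are possibilities there and not stated rules. Each miss left out also delays the 10-miss stop by one.

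**4. Illustration under an assumption.** The protocol does not say how many cases would reach these rulings. Suppose a share d of true misses is ruled out and enrolment continues to 368 events. With true sensitivity s, the chance of a clean 368/368 is [s / (s + (1 − s)(1 − d))]^368.

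| s | d = 0 | d = 0.25 | d = 0.5 | d = 0.75 |
|---|---|---|---|---|
| 99.0% | 2.5% | 6.2% | 15.7% | 39.5% |

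At s = 99.5% the chance is 15.8% for d = 0 and 39.7% for d = 0.5. These figures show how strongly the result depends on d. They do not estimate d.

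**5. Which primary events are exposed.**

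- Craniotomy, fracture elevation and pressure monitoring: no liaison causality ruling.
- Death and intubation: liaison ruling, with causality presumed.
- Injuries found through discharge review or radiology logs: liaison ruling with no stated default. The discharge search runs to three months after each study period, whereas the primary definition requires the event within seven days of injury, so only part of these cases can count.

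**The case against.** A reader might infer that a liaison can strike a miss from the record and so turn a failed validation into a success, or that the whole primary result rests on unblinded discretion. The documents do not support either reading.

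- Section 4.3.8.2 does not say that protocol-error cases are removed. The exclusions in 4.3.8.1 cover cases never entered in the database and suspect records of a suspended physician. Section 4.3.5.1.2 says that wrongly diagnosed cases are reclassified, which points to keeping them.
- The same section defines a false negative, if loosely, and sends both the missed injury and the review finding to UCLA. Completed surveys cannot be altered at the site (4.3.6), and UCLA runs the analysis (4.3.1), so a label can be checked against the locked record.
- The presumption of causality pushes towards counting deaths and intubations.
- Liaison knowledge of the classification is not settled. Section 4.3.8.3 restricts access codes. Section 4.3.4 destroys the study-number slips once outcomes are collected, while 5.2 keeps a linkage file until quality assurance ends.
- The primary outcome is an estimate with an interval. A clean 368/368 is the sample-size premise, and the study may continue through nine misses.

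All of this stands, and it narrows the exposure. It does not supply a blinding statement for the liaison, a stated consequence for a protocol-error label, or a reason to leave false-negative status to judgment.

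**Conclusion.** The point holds in a limited form. Two rulings that feed the primary sensitivity are left to a liaison not stated to be blind to the instrument result, and one of them concerns a status that can be computed. Most safeguards a reader would look for are present, and the number of affected cases is unknown and probably small. The size per case is firm: at 368 events, one case counted or not counted as a miss separates a lower limit of 99.0% from one of 98.5%, and the same count feeds the 10-miss stop.

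This rests on the exact interval that the protocol specifies and on enrolment ending at 368 events. For the causality ruling, removal from the endpoint is stated. For the protocol-error ruling, removal is only a possibility left open by silence, and that silence is itself the gap. Nothing here suggests that any liaison would misuse the discretion; the concern is that the text does not rule out its influence.

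**What to change.** 1. **4.3.8.2.** Have the core UCLA team derive false-negative status from the locked survey record and the neurosurgical definition in 4.3.5.1.2, in place of liaison judgment. State that a protocol error identified after the outcome is known is flagged but stays in the primary sensitivity and in the 10-miss count. Add a sensitivity analysis that excludes flagged cases.
2. **4.3.5.1.2.** State that the liaison judges causality of death or intubation without the survey responses or the instrument classification. Keep the existing presumption of causality. Review by another site's liaison is optional; it would add a data flow between sites and is not needed for this fix.
3. **4.3.6 and 4.3.8.3.** Reconcile what liaisons may see. Since item 1 needs a link between a later-found injury and its survey, settle at the same time whether the linkage is destroyed early (4.3.4) or kept until quality assurance is complete (5.2).

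The cost is protocol wording, with no new staff and no extra patients. The downside is that true protocol errors remain in the primary estimate, which may be slightly less favourable; the sensitivity analysis shows by how much.
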